### Baseline assessment of subjects

After recruitment, the subjects will undergo baseline assessment to collect information on their main characteristics before intervention. A descriptive exploratory questionnaire will be administered to collect information on i) demographic and socioeconomic variables (gender, age, socioeconomic status, education, skin color and marital status); ii) behavioral variables (physical activity measured by the International Physical Activity Questionnaire (www.ipaq.ki.se), smoking status, and alcohol consumption); iii) anthropometric variables (body weight, height, and waist circumference); iv) clinical variables (BP and use of antihypertensive medication); and v) quality of life assessed by the Medical Outcomes Study 36-Item Short Form Health Survey (SF-36) [42]. Eligible individuals who are willing to participate will be instructed to fast for 8 h and come for a scheduled second visit at the study site. In this visit, subjects will have blood samples collected for blood testing, in addition to the assessment of FMD of the brachial artery and ambulatory blood pressure monitoring (ABPM) cuff placement. A snack will be offered at the end of this visit. In the third visit, the ABPM cuff will be removed and subjects will undergo physical fitness tests (VO_2_max). In the fourth visit, 1-RM testing will be conducted. Subjects who did not show up for the scheduled visits will be contacted again. All blood samples will be collected by a nurse technician. All assessment procedures will be supervised by the study investigators and ICFUC medical staff.

### Assessments

#### Blood collection

Blood collection and testing will be performed at the ICFUC. Subjects’ blood will be collected after a fast of 8 h. The blood sample will be tested for biochemical screening (lipid profile, glucose, glycated hemoglobin, and creatinine), number of EPCs and number of circulating endothelial microparticles. In addition, blood rheology will be assessed for potential changes in the sample studied including increased blood viscosity, reduced red blood cell (RBC) deformability, increased RBC aggregation, fibrinogen levels, and erythrocyte sedimentation rate (ESR).

### Progenitor cell and endothelial progenitor cell count

A 15-ml blood sample for the EPCs will be collected in a Sodium Heparin Vacutainer™ tube. Peripheral blood mononuclear cells (PBMC) will be isolated using Ficoll-Paque (GE Heathcare Life Sciences, Uppsala, Sweden). Progenitor cells (PCs) will be defined as CD34+/CD45dim, and EPCs as CD34+/KDR+/CD45dim. Briefly, blood samples will be diluted once with phosphate buffered saline (PBS) and layered onto Ficoll-Paque in 15-ml conical tubes (BD Biosciences, San Jose, CA, USA). Each tube will be centrifuged at 400 xg for 30 min (Eppendorf-5810, Hamburg, Germany), and the PBMCs at the interface will be collected. Cells will be washed once with RPMI-1640 medium (Gibco™, Vancouver, Canada); stained with 5 μl of antihuman-CD45 FITC, 5 μl of antihuman-CD34 PE (clone 6G12), and 8 ul of antihuman-KDR-Alexa Fluor 647 (BD Biosciences, San Jose CA, USA); and incubated in the dark for 30 min, followed by the addition of 500 μl of PBS until resuspension and acquisition in a flow cytometer (FACSCalibur, CellQuest software, BD Biosciences, San Diego, CA, USA). The total number of events recorded on the mononuclear cells gate was 200,000. The percentage of CD34+ cells was calculated based on the measured number of leukocytes (CD45+ cells) using the ISHAGE (International Society for Hematotherapy and Graft Engineering) gating strategy [43].

### Circulating endothelial microparticles count

A 5-ml blood sample for circulating endothelial microparticles will be collected in a Citrate Vacutainer™ tube. These samples will be analyzed for CD31+/CD41- and CD144+. Initially, the blood will be rendered to separate the platelet-rich plasma and the platelet-poor plasma. All blood samples will be subjected to a two-step protocol centrifugation (860 xg for 15 min at 4 °C, followed by 1700 xg for 5 min at 20 °C) before being stored at -80 °C. Phenotype analysis of the endothelial microparticles will be subsequently performed on samples thawed using a flow cytometer Fluorescence Activated Cell Analyser (FACScanto II da BD Biosciences, San Jose, CA, USA) and the results analyzed with the BD FACS Diva software (BD). For phenotyping of the endothelial microparticles, the following antibodies will be used: anti-CD31+ PE, anti-CD41+ PC7, and anti-CD144+ PE. Endothelial microparticles will be defined as elements with size > 0.1 and < 1.0 μm and showing surface markers CD31+/CD41- and CD144+ [44].

### Assessment of flow-mediated dilation (FMD)

Endothelial function will be measured noninvasively by using brachial artery ultrasound (EnVisor series, Philips Ultrasound, Bothell, WA, USA). This assessment will be performed with a 7 to 12 MHz linear transducer in a heated room at 21 to 24 °C at ICFUC. A software program will be used for two-dimensional color-Doppler imaging acquisition with a simultaneously recorded electrocardiogram (ECG). Image data will be recorded on a DVD. To minimize operational errors, the subject’s arm, and the ultrasound transducer will be positioned and maintained in the same position during the procedure. Baseline images will be recorded. A cuff will be placed around the forearm and inflated to 50 mmHg above systolic pressure for at least 5 min and then removed. Longitudinal ultrasound images of the brachial artery walls will be acquired to assess endothelium-dependent vasodilation. The expected coefficient of variation between the images will be 1.8 to 5.0 %. Flow-dependent vasodilation responses will be expressed as the percentage change in the brachial diameter [36].

### Echocardiography

Echocardiography is a noninvasive imaging approach that uses ultrasound to assess the structures and functioning of the heart; it measures the chamber size and mobility of the walls, valve structures, ejection fraction, diastolic dysfunction parameters, and the direction and speed of blood flowing through the heart chambers. Medical personnel at ICFUC accredited by the Brazilian Society of Echocardiography and blinded to intervention allocation will perform transthoracic echocardiograms with image acquisition in second-harmonic generation with the use of ACUSON SC2000 equipment and a 3 to 12 MHz transducer (Siemens). This data will be digitally stored for further analysis by more experienced evaluators.

### Blood pressure

Two different approaches will be used to evaluate the BP levels: clinical assessment and ambulatory blood pressure monitoring (AMBP). The clinical assessment will consist of acute and subacute BP measurements as a way to evaluate exercise responses. Measurements will be taken with the subject in a sitting position using a semi-automatic sphygmomanometer (Omron 705CP). BP levels will be measured in both arms in the pre-study assessments, and the arm with highest values will be used for measurements in the study. Subacute clinical assessments will be conducted at the following time points: before the beginning of each training session (pre-exercise), immediately after exercise (early post-exercise), and 20 min after the end of each session (late post-exercise). ABPM will be performed in all study groups before the first exercise session and at the completion of the entire training intervention. Blood pressure measurements will be obtained from an oscillometric Dina-map™ device. Both assessments will follow the VI Brazilian National Guidelines in Cardiology [40].

### Functional capacity

VO_2_max will be obtained from a cardiopulmonary exercise test using a cycle ergometer and 12-lead ECG monitoring supervised by a cardiologist. Gas exchange measurements will be taken with the use of an ergo spirometer (VO2000 model, Inbramed, Porto Alegre, Brazil). This device collects exhaled gas samples and can store data acquired with each breath (breath-by-breath). Heart rate will be monitored with a frequency meter (Polar S610 model) as follows: online heart rate readings, determination of maximum heart rate at each exercise stage, and stopwatch with partial times. The maximal exercise test will be scheduled at least 48 h in advance. Upon participant arrival at the study site, BP levels will be measured according to the study protocol. Subjects will be asked to sit on a chair, and a facemask (or nozzle) and a frequency meter will be attached. Resting VO_2_ and VCO_2_ measurements will be taken, and the test will be started only when the respiratory exchange ratio (RER) is lower than 0.95. The test will be stopped when the subjects are exhausted and signal that they can no longer turn the pedals [45].

### One-repetition maximum strength (1-RM) assessment

The one-repetition maximum strength test (1-RM) will be used to measure the maximum strength. Subjects will warm up on a cycle ergometer for 5 min. They will then be instructed to perform the maximum number of repetitions with a given load until they can perform only one lift of a load in up to five attempts to achieve the maximum load. A rest period of 3 to 5 min will be provided between each attempt, so rest intervals are of sufficient length to allow the restoration of energy reserves [46]. The same procedure will be followed for all types of strength exercises proposed in the study (leg press, bench press, knee extension, biceps curl, knee bend, and low row). The speed of movements will be controlled with a metronome in both intervention protocols. Exercises will be performed at a pace of 2 seconds for both concentric and eccentric phases. This test will take place at three time points: during the first 2 weeks (60 % of 1-RM); during the intermediate weeks (70 % of 1-RM); and at the end of week 8 (80 % of 1-RM) to maintain exercise at an appropriate intensity throughout the protocol.

### Intervention protocols

The study intervention will comprise 12 weeks of exercise sessions, lasting on average 50 min, three times a week. Exercise sessions will include a warm-up period of 5 to 10 min at the beginning, resistance or combined aerobic exercises for 40 min, and a cool down/relaxation period.

AT will be performed on a cycle ergometer for the entire intervention. Subjects will be monitored with heart rate monitors (Table 4).

**Table 4 Tab4:** Intensity and duration of aerobic training on a stationary bike during a 12-week intervention

	Phase I	Phase II	Phase III
Intensity	50 to 65 % HRR	55 to 70 % HRR	60 to 75 % HRR
Session duration	40 min	40 min	40 min
Exercise duration (weeks)	4	4	4

HRR, heart rate reserve

RT will include six types of exercises that alternate between large and small muscle groups (leg press, bench press, knee extension, biceps curl, knee bend, and low row) for the entire training intervention (Table 5).

**Table 5 Tab5:** Intensity, number of sets, repetitions, rest period between sets, and session duration of resistance training during a 12-week intervention

	Phase I	Phase II	Phase III
Intensity	60 % 1-RM	70 % 1-RM	80 % 1-RM
Sets	4	4	4
Repetitions	10 to 12	8 to 10	6 to 8
Rest period between sets	60 s	60 s	90 s
Session duration	40 min	40 min	40 min
Exercise duration (weeks)	4	4	4

1-RM, one-repetition maximum strength test

CT will consist of resistance and aerobic exercises combined in one session performed over a 40-min period set as in the other two protocols, so that training volume is similar across all intervention groups for the entire intervention (Table 6).

**Table 6 Tab6:** Intensity, number of sets, repetitions, rest period between sets, and session duration of concurrent training during a 12-week intervention

	Phase I	Phase II	Phase III
Resistance training			
Intensity	60 % 1-RM	70 % 1-RM	80 % 1-RM
Sets	2	2	2
Repetitions	10 to 12	8 to 10	6 to 8
Rest period between sets	60 s	60 s	90 s
Session duration	20 min	20 min	20 min
Aerobic training			
Intensity	50 to 65 % HRR	55 to 70 % HRR	60 to 75 % HRR
Session duration	20 min	20 min	20 min
Exercise duration (weeks)	4	4	4

1-RM, one-repetition maximum strength test; HRR, heart rate reserve

A basic training principle is the progression of exercise intensity, duration, or frequency. Progression of exercise in the study intervention will be through gradual exertion increase for the protocols [46]. Borg’s rating scale of perceived exertion (6 to 20 point scale) will be used to help control the training intensities [47]. All subjects will be allowed an initial adjustment period. Those with resting BP levels higher than 160 mmHg (SBP) and/or 105 mmHg (DBP) before cardiopulmonary testing, 1-RM, or an exercise session (AT, RT and CT) will not be allowed to participate in any activities [40]. Those experiencing BP higher than the recommended level on a second occasion will be referred to the study cardiologist for evaluation. The cardiologist will determine whether the subject can continue participating in the study.

Subjects diagnosed with SAH and diabetes mellitus type 2 will have their blood glucose checked (Optium Xceed, Abbott Diabetes Care, Inc., Alameda, CA, USA) in addition to BP measurements before cardiopulmonary exercise testing, 1-RM or an exercise session (AT, RT, and CT) and every 15 min throughout exercise sessions. If the blood glucose levels are lower than 100 mg/dL during cardiopulmonary exercise testing, 1-RM, or exercise sessions (AT, RT and CT), subjects will receive 30 to 45 g glucose gel (Gli-Instan, Lightsweet ™) to maintain levels above 120 mg/dL, and their blood glucose will be checked again 15 min later. Those with blood glucose higher than 250 mg/dL will have their urine tested for the presence of ketones (ComboStik™, Gyung-Nam, Korea), and they will be allowed to resume exercise only if test results are negative. Subjects with blood glucose lower than 100 mg/dL during exercise sessions will have to discontinue exercising and be offered a snack. Their blood glucose will be tested again 15 min later, and they will be allowed to resume exercise only if their test results are acceptable [48].

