### Sample selection

The study sample will comprise individuals with no history of cardiovascular disease (except for SAH controlled with the use of medications), neuromuscular, endocrine, and/or metabolic conditions (except for diabetes mellitus type 2) who are attending the IC health care facilities.

Subjects will be selected based on information collected from their medical records. Eligible individuals will be contacted by telephone and informed of the purpose and procedures of the study. For those willing to participate, a first visit will be scheduled when a clinical questionnaire will be administered, and they will be asked to sign a free informed consent form to participate in the study. Other study visits will be scheduled for those meeting the inclusion criteria of the study (Table 3).

**Table 3 Tab3:** Inclusion and exclusion criteria for the study

Inclusion criteria	Exclusion criteria
• Males and females aged 18 to 70 years • Diagnosed with SAH • Signed a free informed consent form • Considered insufficiently active (IPAQ) • Non-active smokers	• Currently engaging in any type of systematic physical activity • Blood pressure hyper-reactivity in the clinical assessment (SBP > 220 mmHg and/or increase in DBP > 15 mmHg) • Ongoing infectious diseases • Obesity class II or III (BMI) • Heart failure class III or IV; recent cardiovascular event (in the last three months); chronic renal failure; and malignant disease with life expectancy < 2 years • Orthopedic impairments or any physical or mental limitations that prevent physical exercises • After the training intervention, individuals who attended < 85 % or missed > 2 consecutive training sessions will be excluded from the sample. Subjects will be encouraged to complete any missed session at the end of training by performing additional sessions.

SAH, systemic arterial hypertension; IPAQ, International Physical Activity Questionnaire; SBP, systolic blood pressure; DBP, diastolic blood pressure; BMI, body mass index

The following formula will be used for the calculation of sample size (n_p_) to estimate the number of hypertensive individuals to be included in the study:$$ \left({\upmu}_{\mathrm{p}}\right):\ {\mathrm{n}}_{\mathrm{p}0} = {\mathrm{s}}^2/\ {\left({\upmu}_{\mathrm{p}}\hbox{-}\ {\mathrm{x}}_{\mathrm{p}}\right)}^2\mathrm{x}\ {\left({\mathrm{t}}_{\upalpha; \mathrm{g}\mathrm{l}}\right)}^2, $$

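### Table 3's attendance exclusion also removes randomised subjects whose sessions the protocol's own blood pressure rule withheld, which ties exclusion to a secondary outcome; the expected effect is small

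*Protocol article*

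**What the plan says.** Table 3 (Sample selection) lists, among the exclusion criteria, a rule applied after randomisation: "After the training intervention, individuals who attended < 85 % or missed > 2 consecutive training sessions will be excluded from the sample". It names no cause of absence that is exempt. Its one relief is that "Subjects will be encouraged to complete any missed session at the end of training by performing additional sessions".

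The Intervention protocols section adds a safety rule. A subject whose resting pressure is above 160 mmHg systolic and/or 105 mmHg diastolic before an exercise test or a session "will not be allowed to participate in any activities". Then: "Those experiencing BP higher than the recommended level on a second occasion will be referred to the study cardiologist for evaluation". The next sentence is: "The cardiologist will determine whether the subject can continue participating in the study".

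The study population is limited to people without cardiovascular disease "except for SAH controlled with the use of medications". No blood pressure cut-off for control is given. Flow-mediated dilation (FMD), endothelial progenitor cells and microparticles are the primary outcomes in Table 1; blood pressure, in the clinic and by ambulatory monitoring (ABPM), is secondary in Table 2.

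**The concern.** The attendance exclusion does not ask why a session was missed. A subject who was willing to train, and was kept from it by the protocol's own limit, is removed in the same way as one who stopped coming. Because the limit is a blood pressure reading during follow-up, leaving the sample then depends on an outcome variable. If one type of training lowers pressure less than another, its arm will produce more high readings and lose more subjects, although the rule is identical in all three arms.

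At stake are the randomised comparison, some precision with only 27 per arm, and the comparison of blood pressure after training. The main primary outcomes are affected too: FMD and the cell and microparticle counts are measured at rest or from blood, so a subject unfit to train could still contribute them.

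**Working it through.** **What triggers exclusion.** Sessions: 12 weeks × 3 = 36. 85 % of 36 = 30.6, so at least 31 must be attended and a sixth miss excludes. A third consecutive miss also excludes. A subject stopped for good at session s misses sessions s to 36, which is 37 − s in a row. More than 2 means 37 − s ≥ 3, so s ≤ 34. Only a stop at one of the last two sessions escapes. Make-up sessions can repair isolated misses but not a permanent stop.

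**Planned size.** 27 per arm. The article's formula gives it if 0.05 is read as a standard deviation and the error as 0.02: (0.05² / 0.02²) × 2.069² = 6.25 × 4.281 = 26.75, and 3 × 26.75 = 80.3, rounded to 81.

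**How many subjects, and with what effect.** The article gives no rate of repeated high readings, so this part rests on assumptions:
- Systolic pressure only; true baseline mean 130, 135 or 140 mmHg, SD 10, cut off at 140 or 150 to represent controlled hypertension.
- Reading SD 8 mmHg; 38 checks (36 sessions and two exercise tests).
- Two arms with true training effects of −8 and −3 mmHg (SD 5), building linearly over 36 sessions, so the true difference is 5 mmHg.
- Referral when at least 2 checks exceed 160; every referred subject is removed (an upper case).

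The standard-error ratio is √[(1/n₁ + 1/n₂) / (2/27)], with n = 27 × (1 − share referred). Example: shares of 6.3 % and 11.4 % give n₁ = 25.3 and n₂ = 23.9, hence √(0.0813 / 0.0741) = 1.048.

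Results with 300,000 simulated subjects per arm (simulation error in the mm Hg columns is a few hundredths):

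| Cut-off, baseline mean | Referred, % | Referred, of 27 | SE ratio | Difference in change, excluded | Difference in post-training level, excluded | Difference in change, kept as randomised but training stopped |
|---|---|---|---|---|---|---|
| 140, any mean | at most 0.08 v 0.39 | 0.0 v 0.1 or fewer | 1.001 | 4.97 to 4.99 | close to 5 | close to 5 |
| 150, 130 | 1.6 v 3.2 | 0.4 v 0.9 | 1.012 | 4.94 | 4.7 | 4.95 |
| 150, 135 | 3.5 v 6.6 | 0.9 v 1.8 | 1.026 | 4.89 | 4.5 | 4.87 |
| 150, 140 | 6.3 v 11.4 | 1.7 v 3.1 | 1.048 | 4.82 | 4.3 | 4.82 |

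Of those referred, 83 to 97 % reach their second high reading by session 34. If the cardiologist stops nobody, withheld sessions alone meet Table 3 in 0.3 or fewer of 27 per arm, before any make-up session.

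**Sensitivity to reading SD.** At SD 6, at most 0.3 v 0.9 of 27 are referred. At SD 10 with cut-off 150, it is up to 4.5 v 6.5, and the standard error rises by 12 %.

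**FMD.** If the true arm difference is 1 percentage point, the SD of change 3 and the correlation with the fall in blood pressure 0.6 (all assumed), the bias is about 0.07 points or less.

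**A check that does not use the simulation.** If 2, 5 or 10 % of subjects are lost, n per arm falls from 27 to 26.5, 25.7 or 24.3. The pairwise difference detectable with 80 % power, (1.960 + 0.842) × √(2/n), goes from 0.762 SD to 0.770, 0.782 or 0.804 SD.

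**The case against.** The strongest objection is that the remedy hardly changes the estimate. On change in blood pressure, removing the stopped subjects and keeping them with incomplete training give nearly the same arm difference, as the table shows. This stands at reading SD 8. What keeping them gains is the comparison as randomised, some precision and less bias on post-training level.

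Second, the figures are upper cases. Referral is to an evaluation, and the cardiologist may let the subject go on. With a cut-off of 140, a natural reading of controlled hypertension, almost nobody is referred. A check that averages two readings would lower the counts further. This also stands, and it is why the point ranks low.

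Third, a reader might infer that the outcome assessments of a stopped subject are not done, because "ABPM will be performed in all study groups before the first exercise session and at the completion of the entire training intervention". The article does not support that. The sentence is a schedule for the groups; it does not make one subject's monitoring conditional on finishing, and nothing cancels FMD or blood sampling. What is stated is exclusion from the sample. Nor does the sentence on the cardiologist's decision show that a stopped subject is withdrawn from follow-up. It is ordinary safety wording and may mean training only, and Table 3 excludes the subject on either reading.

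Fourth, this is one narrow route into a wider fault: the attendance rule excludes for every cause of absence. That is correct, so the change belongs in Table 3 and should not be a special exemption for blood pressure.

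**Conclusion.** The point holds as a minor one. Table 3 states an exclusion after randomisation, whatever the cause of absence, and the blood pressure limit makes part of it depend on a secondary outcome. This is in the printed text and is not a detail left to a fuller document.

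Its size rests on assumptions, since the article gives no rate of repeated high readings, no definition of control and no rate of stopping. With controlled hypertension and a reading SD of 8 mmHg, the bias in the arm difference in change is negligible (at most about 0.2 of 5 mmHg) and the loss of precision about 0 to 5 %. The bias is larger only on post-training level, up to about 0.7 of 5 mmHg (5 − 4.3). The larger loss of precision needs a reading SD of 10, the 150 cut-off and removal of everyone referred, all together. A claim that the rule would seriously distort the comparison of training types goes beyond what the documents support.

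**What to change.** In Table 3, replace the exclusion with a statement that the main analysis keeps all randomised subjects with post-training data in their allocated arm, including those stopped on medical grounds. Let the attendance rule define only a supplementary analysis of adherent subjects.

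In Intervention protocols, say that the cardiologist decides whether training and exercise testing may continue. Add that a stopped subject still attends the planned week-12 resting assessments (FMD, blood, ABPM) unless consent is withdrawn or attendance is medically inadvisable. The 160/105 mmHg limits stay.

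The cost is about one sentence in each place and no new visit. The downside is slight dilution from incomplete training: at most about 0.2 of 5 mmHg at reading SD 8 if every referred subject stops for good, and more if referrals are as frequent as in the SD 10 case. The supplementary analysis still describes those who completed the training.

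### Two unlinked instructions cover one event, blood glucose below 100 mg/dL during an exercise session in subjects with type 2 diabetes

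*Protocol article*

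**What the plan says.** The relevant text is the last paragraph of Intervention protocols in the protocol article. It applies to one subgroup: "Subjects diagnosed with SAH and diabetes mellitus type 2 will have their blood glucose checked". Checks are required before cardiopulmonary testing, before 1-RM testing and before each AT, RT or CT session, and then "every 15 min throughout exercise sessions".

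Two instructions for low readings follow, separated by the rule for readings above 250 mg/dL.

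- **First instruction.** It covers cardiopulmonary testing, 1-RM testing and training sessions, and its trigger is a reading under 100 mg/dL during any of these. The action is that "subjects will receive 30 to 45 g glucose gel" "to maintain levels above 120 mg/dL, and their blood glucose will be checked again 15 min later".
- **Second instruction.** "Subjects with blood glucose lower than 100 mg/dL during exercise sessions will have to discontinue exercising and be offered a snack". A retest follows after 15 min, and "they will be allowed to resume exercise only if their test results are acceptable".

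Sample selection expressly admits people with type 2 diabetes, so the subgroup can occur in the trial. Its size is not stated.

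**The concern.** Threshold, subgroup and one setting (the training session) are the same in both instructions, but the prescribed actions differ. A member of staff who sees a reading under 100 mg/dL in mid-session finds one sentence about gel and another about stopping and a snack. Nothing ranks them, joins them or assigns them to different moments.

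What is at stake is first the safety of participants, because this is a rule for supervising exercise in people with diabetes. Second comes uniform delivery of training: the article intends similar training volume across the three groups, and whether a session is interrupted is part of what is delivered.

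**Working it through.** No sample size, power or event count enters this point, so the check is a comparison of the two instructions.

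| Element | First instruction | Second instruction |
|---|---|---|
| Subgroup | SAH with type 2 diabetes | Same |
| Trigger | Below 100 mg/dL | Below 100 mg/dL |
| Setting | Cardiopulmonary test, 1-RM, training session | Training session only |
| Carbohydrate | Gel, 30 to 45 g | Snack, no quantity |
| Stopping exercise | Not addressed | Required |
| Level named | Above 120 mg/dL, as the aim of the gel | None |
| Recheck | 15 min | 15 min |
| Condition for resuming | None stated | Result must be acceptable; no number |

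Three situations show where the text leaves staff without a single answer. The readings are illustrations, not data.

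1. **95 mg/dL during a training session.** Both triggers are met. One person may give gel, citing the first sentence. Another may stop the session and offer a snack, citing the second. A third may do all of it. The article does not say which is meant.
2. **110 mg/dL at the 15-min retest.** This is above the trigger (110 > 100) but below the stated target (110 < 120). If acceptable means no longer under the trigger, exercise resumes. If it means the 120 mg/dL target has been reached, it does not. Every retest from 100 to 120 mg/dL is open in this way.
3. **95 mg/dL at the check before a session.** The check is required, but both low-glucose instructions are worded for readings during the activity. No action is stated. One of the two sentences may have been meant for this time point, but the text does not say so.

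**Extent.** Three sessions a week for 12 weeks gives 3 × 12 = 36 scheduled sessions per subject. That is the upper limit on sessions in which the rule could be invoked for one diabetic subject. The number in which it is invoked depends on how often readings fall below 100 mg/dL, which the article does not give.

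**Effect within one session.** Under the second instruction a stop lasts at least until the 15-min retest. Against the 40-min exercise block that is 15/40 = 37.5 %, if the time is not added back; the article does not say whether it is. Under a gel-only reading of the first instruction there need be no pause.

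**The case against.** The strongest reply is that the sentences are compatible: stop, give gel, offer a snack, retest at 15 min. Neither forbids what the other requires. On this view the first sentence deals with carbohydrate in three settings, and the second adds stopping and resuming for training sessions. It stands to this extent: a reader might infer that staff cannot follow both instructions, and the text does not support that. It does not remove the ambiguity, because the article nowhere says the actions are combined, and a combined reading still leaves the 100 to 120 mg/dL range unresolved.

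Other stronger readings also fail.

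- **That the first instruction tells subjects to keep exercising.** It is silent on stopping. The only statement on stopping for low glucose in training sessions is in the second.
- **That there are two competing conditions for resuming.** Only the second instruction has one. The 120 mg/dL figure is what the gel is meant to maintain. The gap is that its relation to an acceptable result is not stated.
- **That every session of a diabetic subject is affected.** Glucose is checked around every session, but the instructions matter only after a reading below 100 mg/dL.
- **That the rule changes who stays in the sample through the attendance criterion.** Table 3 counts sessions attended and consecutive sessions missed, not minutes completed, and it encourages missed sessions to be made up. Nothing says an interrupted session counts as missed.

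Finally, a journal article may leave operational detail to the full protocol, and the closing sentence cites a source that is not available here. Taken alone, the undefined word would be such a detail. But the article chose to state this rule in full and stated it twice with different actions. That is an inconsistency in the text shown.

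**Conclusion.** The point holds as an ambiguity in a stated safety rule. One event carries two unlinked instructions, the 120 mg/dL target is not tied to the condition for resuming, and no action is given for a low value at the required check before a session. The same reading can be handled differently by different staff.

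The conclusion rests only on the wording of the one paragraph and assumes that no other document available to staff already resolves it. Its practical size is unknown beyond the ceiling of 36 scheduled sessions per diabetic subject. No effect on sample size, error rates or the set of subjects analysed is shown. It should be corrected because it concerns safety and is cheap to correct. Nothing here implies a view on which clinical instruction is right.

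**What to change.** The study physicians should reconcile the two sentences into one consistent rule for each setting and time point: the check before a session, testing (cardiopulmonary and 1-RM), and the training session. Each rule needs a single stated action, saying explicitly if several steps are to be taken together, and a defined condition for resuming, so that the 120 mg/dL target and the release condition are either linked or kept clearly apart. The choice of action and values is theirs; none is proposed here.

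The cost is a short protocol clarification and a notice to the staff who supervise sessions and tests. The article gives the trial's status as recruiting, so the clarification should be dated. No change to the design, sample size or analysis is needed.
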